#### Costs of implementation strategies

We will compare the costs of using REP versus enhanced REP for spreading and sustaining CTI. We conceptualize the adaptation of CTI to aftercare as a fixed, non-repeatable cost that will not be included in our analyses. Most costs associated with the spread stage of implementation are fixed, repeated with each cohort, including CTI initial training, communities of practice, and toolkit maintenance; these costs will be assessed by cohort. Variable spread costs that depend on the number of sites per cohort include case consultation and EF; these will be assessed by the site. With respect to sustainment, the quarterly booster sessions and re-training of new case managers at the participating implementation sites are repeatable fixed costs. Case manager turnover will be tracked using the national roster of aftercare participants per case manager.

All implementation activities of our team will be tracked through the Implementation Activity Log. In addition, to capture time spent by the implementation team on session preparation or documentation (i.e., time that is not captured in the Implementation Activity Log), team members will complete cost capture templates weekly during the second implementation cohort. Implementation activity log and cost capture template data will be linked to hourly costs per team member.

#### ROI of CTI and implementation strategies

The financial ROI of CTI and these implementation strategies depends on savings reaped through improved housing stability and decreased hospitalizations. To calculate the degree of cost offsets, we will link HEVs’ use of VA housing and health services to the costs of these activities which are available in an activity-based cost allocation system (the Managerial Cost Accounting System) [28]. Among HEVs who enroll at implementation sites between 6 and 18 months after the initiation of CTI implementation, we will calculate mean housing and health services costs per HEV in the 6, 12, and 18 months after enrollment. We will use a multivariable generalized linear model and two-part regression models where appropriate to compute ROI at 6-, 12-, and 18-month time horizons for HEVs in sites that received REP versus enhanced REP, and compared to the 32 control sites. We will compare model fit using a generalized linear model and ordinary least squares [29].

### Contextual factors

Using data from semi-structured interviews with aftercare case managers and supervisors, and periodic reflections with aftercare liaisons and Housing Transitions QUERI staff engaged in implementation, we will assess CFIR-based contextual factors relevant to CTI, including provider and site characteristics, inner setting and outer context, perceived veteran needs, and perceived characteristics of CTI, REP, and enhanced REP. We will integrate these data with our assessments of fidelity, sustainment, quality metrics, costs, and ROI to explore potential relationships.

### Qualitative data collection

Table 4 summarizes our planned qualitative data collection, detailed below.

**Table 4 Tab4:** Summary of qualitative data collection

	Sample size	Timing^**a**^	Duration
**Interviews**			
Aftercare case managers and supervisors	50 (16–17/cohort)	Baseline^b^, 12 and 18 months	45 min
HEVs enrolled pre-CTI implementation	30 (10/cohort)	Baseline	30–45 min
HEVs enrolled post-CTI implementation	30 (10/cohort)	18 months	
**Periodic reflections**			
Implementation team	~6	Monthly	15–30 min
Aftercare liaisons	18 (6/cohort)	Quarterly	

^a^In relationship to each cohort’s CTI implementation initiation

^b^Post-initial CTI training but prior to implementation

#### Aftercare staff semi-structured interviews

As described above, we will conduct semi-structured interviews with aftercare staff (~50, or 16–17/cohort, including liaisons, supervisors, and case managers) engaged in CTI implementation across the 32 sites. We will use maximum variation sampling [30] to ensure diversity by geography (urban, suburban, rural) and the number of case managers per site. Interviews will be conducted, by cohort, at baseline (during and post-CTI training) and 12 and 18 months post-implementation. At baseline, we will assess staff background, education, and training; baseline practices; contextual factors (e.g., site-specific characteristics); and knowledge, prior experiences with and perceptions of CTI, and expectations about CTI implementation barriers and facilitators. Interviews at 12 and 18 months will assess experiences with CTI and with REP and/or enhanced REP, fidelity to CTI’s core components, and recommendations for CTI implementation support. Interviews at 18 months will additionally assess barriers and facilitators to sustainment. Each interview will last ~45 min and will be conducted by videoconference or telephone.

#### HEV semi-structured interviews

We will use the GPD National Program Office’s aftercare roster to identify up to 30 HEVs (10/cohort) who used aftercare in the 6 months prior to implementation, and a different set of 30 HEVs (10/cohort) who used aftercare 12–18 months after implementation. We will use maximum variation sampling [30] to ensure diversity by site and age. We will assess perceived needs from and experiences with the aftercare program. These ~30–45-min interviews will be conducted by telephone.

#### Periodic reflections

Periodic reflections are ethnographically informed, pragmatic, and a low-burden method to observe implementation events and contextual factors among stakeholders over the implementation period. These reflections support consistent documentation of implementation strategies, adaptations, changes to inner and outer settings, unexpected events, and experiences of EBP implementation [25]. Periodic reflections will be conducted monthly with Housing Transitions QUERI staff engaged in CTI implementation and quarterly with a subset (*n*=18, 6 per cohort) of VA liaisons to the aftercare program. We will purposively sample liaisons affiliated with urban, suburban, and rural sites. All reflections (15–30 min/each) will be conducted by telephone or videoconference.

#### Analyses

Analyses of interview and reflection data will employ rapid qualitative analyses [31]. We will create a structured summary for each interview or reflection using templates organized by domains of interest within our conceptual framework; we will develop matrices to synthesize content by site, cohort, and participant, before completing summary tabulation tables to validate patterns identified in the data and ensure the trustworthiness of findings. We will conduct targeted in-depth coding and analyses as needed, using the constant comparison method [32] and ATLAS.ti software to confirm/disconfirm exploratory hypotheses or explore emergent data patterns. Qualitative and quantitative data will be gathered concurrently over the course of implementation and integrated to identify whether/how contextual factors emerging in qualitative data are associated with quantitative implementation outcomes.

### Products to support the continued spread and sustainment of CTI in aftercare

Though the scope of this project is to implement CTI in 32 sites, our overall goal is to support our partners in using knowledge from this project to implement and sustain CTI in all 128 aftercare sites. Therefore, we will package the findings and products from this project into a business case analysis and implementation playbook.

### Business case analysis

We will use findings from our implementation evaluation to prepare a business case analysis of the costs, cost offsets, and non-financial benefits of CTI sustainment and spread in aftercare and the business case for REP versus enhanced REP. These analyses will be prepared from the perspective of VA’s Homeless Program Office, which oversees aftercare and pays for its services. Table 5 displays expected CTI costs (for spread/sustainment and care delivery) and benefits (cost offsets and non-financial evaluation). Our evaluation estimates the magnitude and features of these costs and benefits. We will assess whether enhanced REP’s investment in EF yields a sufficient combination of downstream financial cost offsets and non-financial benefits to justify enhanced REP as the preferred strategy, over REP alone, to spread and sustain CTI. We will also provide information about aftercare contextual factors that may signal an above-average benefit from enhanced REP versus REP.

**Table 5 Tab5:** Expected resources and benefits to be measured for CTI spread and sustainment

Expected resources (costs)		Expected benefits
Spread/Sustainment costs	Care delivery costs	Cost offsets and non-financial benefits
• *Fixed*: Implementation team providing 6-week CTI training, aftercare staff and VA aftercare liaison receiving a 6-week CTI training, Community of Practice webinars, toolkit maintenance, and quarterly CTI booster sessions • *Variable*: Implementation team and aftercare staff time spent giving/receiving case consultation and EF^a^	• *Variable:* Aftercare staff time spent providing CTI^b^; VA provider time associated with increased outpatient mental health, SUD, medical, and vocational service use	• *Cost offset:* decreased use of VA residential housing services; decreased hospitalizations • *Non-financial benefits*: HEVs’ housing stability; HEVs’ receipt of needed mental health, SUD, medical and vocational services; improved HEVs’ care experiences; improved case managers’ experiences providing care

^a^Only applies to aftercare sites receiving enhanced REP to support CTI implementation and sustainment

^b^If there are additional costs associated with using CTI and/or the policy partners were to stop paying for this staff

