### CTI implementation pilot

Housing Transitions QUERI builds on a 1-year implementation pilot in which we developed resources and processes for CTI training and technical assistance (TA) and external facilitation that were piloted and refined at four aftercare sites. We also identified outcome measures for future evaluation. To this end, we formed a virtual stakeholder workgroup comprised of two CTI expert trainers, a faculty consultant from a university-based center with CTI expertise, a VA social worker who served as the “liaison” to the four pilot sites, and a peer provider with professional and lived expertise in GPD programs.

We drew upon this workgroup to tailor a 6-month version of CTI that was previously implemented in Connecticut-based homeless programs [17]. We made practice adaptations to reflect the aftercare context and augmented anonymized cases presented in the training and TA materials to reflect the social circumstances, functioning, and diagnoses of HEVs in aftercare. We made additional adaptations in response to precautions imposed by the coronavirus disease 2019 (COVID-19) pandemic and ensured that all training and TA could be delivered virtually. We also developed an online toolkit [18] with clinical resources, recorded trainings, a CTI manual, and training and TA slide decks.

Next, we pilot-tested this adapted training and TA package (Table 1) with aftercare case managers, supervisors, and our VA social work liaison. First, initial CTI training was delivered in six synchronous videoconferences by national leaders in training and consultation for case managers serving homeless-experienced adults. Next, we initiated a monthly community of practice sessions, i.e., 1-hour discussions to deepen knowledge and expertise in CTI; these sessions included a presentation from the community of practice leader (a social worker on our team) or guest speaker, followed by a moderated discussion among aftercare staff. We also offered individual, on-demand, 30-min case consultations to aftercare staff with a CTI-trained clinician expert on our team.

**Table 1 Tab1:** CTI training and technical assistance (TA) package tailored in the Housing Transitions QUERI implementation pilot

Training/TA component	When is the component delivered?
Six session initial CTI training delivered via synchronous videoconference (2 h/week for 6 weeks)	Once, at the start of CTI implementation, for all aftercare case managers and supervisors

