### Participating sites

Our partners at the GPD National Program Office identified 7 priority VA regions (Veterans Integrated Services Networks [VISNs]) for CTI implementation in aftercare. We will engage with VA homeless program leaders in these VISNs, and their associated VA facilities, to identify 32 aftercare sites across three cohorts, with 10–11 sites per cohort. Sites for each cohort will be identified in the 3 months prior to cohorts’ implementation initiation, based on sites self-identifying as being ready for implementation. Of note, our sample size (32 sites) was pre-determined by our funder.

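### Table 5 books the time trainees spend in the six-week CTI training as a fixed cost, although it rises with sites and staff, so spread costs are mis-scaled for cohorts unlike the trial's

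*Protocol article*

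**What the plan says.** The section on costs of implementation strategies sets out two classes of spread cost. Most are "fixed, repeated with each cohort, including CTI initial training, communities of practice, and toolkit maintenance; these costs will be assessed by cohort". The other class is described thus: "Variable spread costs that depend on the number of sites per cohort include case consultation and EF; these will be assessed by the site". The working test for a variable cost is therefore dependence on the number of sites, and its unit is the site.

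Table 5, in the business case section, applies the split. Its fixed entry covers the team's time providing the six-week training and also "aftercare staff and VA aftercare liaison receiving a 6-week CTI training". Its variable entry is "Implementation team and aftercare staff time spent giving/receiving case consultation and EF".

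Table 1 describes the training: "Six session initial CTI training delivered via synchronous videoconference (2 h/week for 6 weeks"), given once at the start "for all aftercare case managers and supervisors". The section on participating sites plans "to identify 32 aftercare sites across three cohorts, with 10–11 sites per cohort". The section on products gives the wider aim as spread to all 128 aftercare sites.

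**The concern.** Trainers' hours and trainees' hours behave differently. One videoconference series can serve a cohort, so delivery time need not change when a site joins. Attendance time must change, because each new site brings its own case managers and supervisor. By the article's own test, attendance is a variable cost, yet Table 5 puts both under one fixed label. The table is also inconsistent within itself: the same people's time is variable when they receive consultation or facilitation and fixed when they receive training, and no reason is given.

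The business case is a named product of the project (third aim), written for the office that pays for aftercare. Its use is to cost sustainment and further spread, and the fixed/variable split is what carries trial costs over to other numbers of sites. If trainee time sits in the fixed part, the absolute cost of spread and the cost of adding a site will be wrong for any rollout whose cohorts do not resemble the trial's.

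**Working it through.** The article states no wage, trainee count or projected spread cost, so there is no figure to reproduce. The check applies the article's own test and then measures how far the fixed label misleads.

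**Inputs from the article**
- Training hours per trainee (Table 1): 6 × 2 = 12.
- Average sites per trial cohort: 32 / 3 = 10.67.
- Further sites: 128 − 32 = 96.

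**Assumptions**
- Trainees per site, m, are not given; 2, 3 and 5 are used, and m is taken as equal at trial and later sites until the last step.
- Sites per later cohort, s, are not given; several values are tried.
- Liaison time is counted within m. This is a simplification: in the pilot one liaison covered four sites, so liaison hours may rise in steps rather than with each site.

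**Step 1. Does trainee time depend on the number of sites?** A 10-site cohort uses 12 × 10 × m = 120m hours and an 11-site cohort 12 × 11 × m = 132m. The item differs by 132/120 − 1 = 10% between the trial's own two cohort sizes, before any difference in staff per site. It meets the test for a variable cost.

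**Step 2. True trainee hours for 96 further sites.** 12 × 96 × m = 1,152m, whatever the cohort size: 2,304 h at m = 2, 3,456 h at m = 3, 5,760 h at m = 5.

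**Step 3. Hours under the fixed label.** An average trial cohort uses 12 × 10.67 × m = 128m hours. Carried forward as a fixed amount for each of 96/s cohorts, this gives 128m × 96/s.

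**Step 4. Ratio of booked to true hours.** (128m × 96/s) / (1,152m) = 10.67/s, in which m cancels.

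| Sites per later cohort (assumed) | Cohorts | Booked hours | Booked / true |
|---|---|---|---|
| 8 | 12 | 1,536m | 1.33 |
| 10.67 | 9 | 1,152m | 1.00 |
| 16 | 6 | 768m | 0.67 |
| 32 | 3 | 384m | 0.33 |

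**Step 5. Staffing.** If later sites have m′ trainees instead of m, the ratio becomes (10.67/s) × (m/m′). With cohorts of the trial's size but m = 3 and m′ = 2, it is 3/2 = 1.50. The number of case managers is a stratification factor in the trial, so the authors expect sites to differ in it.

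**The case against.** Five points can be made on the other side.

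- **No scaling rule is stated.** The article never says that spread will be costed as the trial's per-cohort figure times a number of later cohorts, and it gives no later cohort size. A reader might infer a three-fold understatement, which is the 32-site row above. The documents do not support that as a property of the plan: the error is nil at the trial's cohort size with like staffing, and it reverses in smaller cohorts. This stands, and the ratios should be read as scenarios.
- **The main comparison is hardly touched.** A reader might infer that REP versus enhanced REP is mis-costed. Both arms receive the same training, so trainee time largely cancels, and facilitation, which differs between arms, is already variable and assessed by site. This stands.
- **The text on costs of implementation strategies may not be wrong.** It says variable costs include consultation and facilitation, which is not a closed list. The tracking it describes is of the team's own activities, linked to team members' hourly costs. Initial training assessed by cohort can therefore be read as delivery time only. This stands as a fair reading, and it confines the plain error to Table 5. It does not rescue Table 5, which names the recipients' time explicitly.
- **Other sessions are not shown to be misbooked.** Table 5 does not say whose time the community of practice and booster entries count, so no error can be asserted there. Nor is a large per-site cost of REP shown, since no wage or trainee count is given, and case consultation under REP is already variable.
- **An article condenses the cost model, and no data are lost.** The Implementation Activity Log records session times and participants, so trainee time can be rescaled later. That makes the repair cheap. It does not turn the point into missing detail, because the article states both the test and a classification that fails it.

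**Conclusion.** The point holds as a classification error in Table 5. Trainee and liaison time in the six-week training is labelled fixed, although it meets the article's own description of a variable spread cost and although the same staff's time receiving other support is labelled variable.

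The consequence is confined to the projected absolute cost of spread and the cost per added site. Trainee hours actually spent in the trial are the same under either label. Size and direction depend on quantities the article does not give: with equal staffing the booked share of true trainee hours is 10.67 divided by the later cohort size, so it may be too high, correct or too low. The ratios also assume that the fixed figure would be carried forward once per cohort, which is what a fixed cost repeated with each cohort implies but which the article does not spell out for spread. The case for or against adding facilitation is largely unaffected. This is worth correcting before costing begins, and it does not threaten the trial's design or primary outcome.

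**What to change.** Split the Table 5 entry. Keep the implementation team's time delivering the training, and toolkit maintenance, as fixed per cohort. Move trainee and liaison time to the variable list, assessed by site as attendee-hours from the Implementation Activity Log multiplied by hourly pay, and scale it by sites and staff when costing spread.

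In the section on costs of implementation strategies, state that initial training assessed by cohort means delivery time only. For community of practice and booster sessions, state whose time is counted; if attendees' time is included, treat it in the same way.

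The cost is a few lines of wording. Session times and participants are already logged, and case manager salary and benefits are already to be obtained for the CTI delivery costs. Pay for supervisors and liaisons is not mentioned there and would have to be added. The downside is that the stated REP cost per added site becomes less favourable.

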### Implementation playbook

We will also develop an online implementation playbook [33, 34], a user-friendly compendium of CTI implementation processes, targets, and outcomes. The playbook will be developed iteratively and collaboratively with our partners to ensure an optimal match between content and partner needs. It will serve as a “how to” guide for spread and sustainment.

The playbook centerpiece will be the finalized CTI package with products generated across REP (e.g., training manuals) and enhanced REP (e.g., facilitation guide). We will iteratively develop guides for these products. The qualitative data collected will provide insights into the nuances of using playbook components and highlight potential adaptations to meet sites’ contextual factors. We will also include implementation “tip sheets,” i.e., small, targeted, informational bytes, to facilitate CTI spread and maintenance. The playbook will also contain copies of leadership briefings and frequently asked questions.

## Discussion

To accelerate VA’s efforts to end Veteran homelessness, we must enhance the implementation and sustainment of EBPs among VA and community providers who serve HEVs. In aftercare, national CTI implementation holds the potential to improve housing and health for one of VA’s most vulnerable populations. Moreover, as case management is one of the primary services offered to HEVs, this project aims to advance the science surrounding strategies that support the implementation and sustainment of effective case management practices. For CTI to be successful at a given aftercare site, an appropriate implementation strategy must be used, considering contextual factors that support and/or impede implementation.

We will use REP to ensure that a robust and stakeholder-informed CTI training and TA package is delivered across 32 aftercare sites. In some settings and contexts, this package may be sufficient to enable CTI implementation and evaluation. However, our cluster-randomized design will allow us to evaluate the business case for adding EF and suggest site-level features that may benefit from this strategy augmentation. Our rollout design, staggering sites’ implementation start dates, allows for a comparative effectiveness-implementation trial of active base and enhanced implementation strategies, balancing training needs with project resources [23]. Though we face implementation challenges—including high rates of staff turnover within human service organizations [35]—we selected a dynamic base implementation strategy that is built on stakeholder engagement [12], which is important in implementation approaches to address homelessness [10].

We note that this implementation initiative was developed in close collaboration with our policy partners; this protocol describes an initiative within a specific VA homeless program, operated by diverse community-based organizations. As such, the findings of our planned implementation-effectiveness evaluation may not extrapolate to other VA or non-VA settings; rather, our goal is to produce products that allow for the continued spread in this setting. The selected sample size (*n*=32) was predetermined by our funder as opposed to deriving from power analyses. Moreover, our selected implementation strategies are robust and stakeholder-informed training and technical assistance (REP and enhanced REP), and external facilitation (enhanced REP); these are costly and time-intensive strategies to support EBP implementation and may not be feasible in low-resource settings.

Regardless of these limitations, for HEVs in aftercare, CTI holds promise as an EBP that can improve this population’s housing and health. The products planned for our policy partners (i.e., business case analysis and implementation playbook) will provide a blueprint for spread to the remainder of aftercare sites, acknowledging the important role of contextual factors in implementation strategy selection. Moreover, understanding effective strategies to support CTI implementation could also support the implementation of other case management practices within and outside VA.

